### Control

During the control steps of the study, participants will receive their usual training allocation. Usual training for staff in the health board involves monthly in-service training on current evidence applied to physiotherapy practice (4 hours per month), weekly technique sessions on the technical & practical skills of physiotherapy practice (30 minutes per week), as well as monthly mentoring sessions observing clinical reasoning (1½ hours per month). Should any of the physiotherapists not receive any or all of the control training, this will be reported, and the reasons why will be discussed.

This choice of control is consistent with other studies into educational interventions using crossover methodologies (Bye et al., 2009, Celebi et al., 2009, Cook et al., 2009, Cook et al., 2006, Murray et al., 1997a, Koles et al., 2005, Lam et al., 2004, Rawlins et al., 2009) where current or traditional practice is used to compare with new or proposed interventions on the basis that the comparison group needs to be plausible and fair (Murray et al., 1997b). Comparisons with "non- intervention" controls are strongly argued against (Cook et al., 2006) on the basis that such studies fail to inform the education community on the issue of selecting the most effective methods from multiple available options; the priority for study is not *whether* students and clinicians can learn using a designated method or combination of methods, but rather how *best* to facilitate learning.

Should any physiotherapists fail to complete the intervention or control elements of the study, this will be reported, as well as the reasons for such failure.

**Figure 4: The dialectical reasoning model. Jones & Edwards, 2007**

[figure not shown]

## Objectives

It is important to clarify the specific objectives and hypotheses for the quantitative component of the trial, and in particular - as this is a CRCT - whether these apply to the cluster level, to the individual level, or to both (Campbell, 2004). . Knowing the level of inference will subsequently aid interpretation of the statistical methods.

### Objectives

It is the objective of the quantitative component of this study to

1. explore whether facilitation of clinical reasoning skills via a clinical mentoring programme delivered to clusters of physiotherapists (outpatient musculoskeletal physiotherapy departments) yields greater improvements in patient outcomes (measured by risk-adjusted patient outcomes measures from clusters of patients at each step) than those yielded with usual training
2. explore whether facilitation of clinical reasoning skills via a clinical mentoring programme relates to improved physiotherapist performance in clinical reasoning, and whether changes in performance correlate with improvements in patient outcomes

### Hypotheses

H: There will be a significant difference in the risk-adjusted outcomes of patients whose physiotherapists have received training in clinical reasoning skills via a clinical mentoring programme when compared with those whose physiotherapists have received standard training.

H: There will be no difference in the risk-adjusted outcomes of patients whose physiotherapists have received training in clinical reasoning skills via a clinical mentoring programme and those whose physiotherapists have received standard training.

H: There will be a significant improvement in the performance of physiotherapists who have received training in clinical reasoning skills via a clinical mentoring programme when compared with their performance having received standard training.

H: There will be no improvement in the performance of physiotherapists who have received training in clinical reasoning skills via a clinical mentoring programme when compared with their performance having received standard training.

H: There will be a correlation between improvements in the performance of physiotherapists who have received training in clinical reasoning skills via a clinical mentoring programme and improvements in the clinical outcomes of their patients.

H: There will be no correlation between improvements in the performance of physiotherapists who have received training in clinical reasoning skills via a clinical mentoring programme and improvements in the clinical outcomes of their patients.

## Outcomes

Clusters of patients will receive their usual physiotherapy treatment after the participating physiotherapists have received either intervention or control training. Outcome data from these clusters will be used to evaluate the effectiveness of the intervention and control training programmes. This data will be collected at the end of each time period to allow for the consolidation and application of the training (which will have been delivered at the start of the time period) to make an impact.

## **Patient Outcome Measures**

In selecting appropriate outcome measures in physiotherapy outcomes research, Jette (Jette, 1993) suggests three important factors to consider - selection of dimensions to measure, psychometric properties and practicality. The selection of dimensions to measure are influenced by the World Health Organization (WHO)'s International Classification of Functioning, Disability and Health (ICF) framework (2001). The ICF is WHO's framework for measuring health and disability at both individual and population levels and was officially endorsed by all 191 WHO Member States in the Fifty-fourth World Health Assembly in 2001 for use in Member States as the international standard to describe and measure health and disability. The use of this framework has been strongly endorsed by multiple authors on the topic of outcome research in physiotherapy (Jette, 2010, Jette et al., 2008, Escorpizo et al., 2010, Mitchell, 2008, WCPT, 2011) on the basis of its common language in describing health states, its systematic and comprehensive classification, and the potential for outcomes measures built from the framework to allow comparison of health and health related states across patients, studies, countries, and clinical services. In particular, the ICF framework has been welcomed in its broadening of focus of outcomes away from the traditional biomedical research paradigm in physiotherapy, beyond mortality and disease, to focus using a more biopsychosocial paradigm on how people live with their conditions (Jette, 2006). In essence, the ICF identifies three levels of human functioning: at the level of body parts, the whole person, and the whole person in their complete environment. Each level, in turn, contains three domains of human function: body functions and structures, activities, and participation (Jette, 2009). The first of these domains - body functions and structures – are defined as such: "In the context of health experience, body functions are the physiological functions of body systems (including psychological functions). Body structures are anatomical parts of the body such as organs, limbs, and their components. Impairments are problems in body function or structure as a significant deviation or loss. Impairments within the ICF include deviations from generally accepted population standards in the biomedical status of the body and its function and can be temporary or permanent." (2001)

Historically, the measurement of impairments has been a key focus of physiotherapy treatment and research (Jette, 2005, Jette, 1995), but the limitations of impairment measurement have more recently been increasingly highlighted on the basis of lack of standardization of impairments and the poor reliability of common measures of impairments (Resnik and Dobrykowski, 2005). As a result, the activities and function domains have been met with enthusiasm within the physiotherapy research literature. The ICF defines an activity outcome as "the execution of a task or action by an individual." and a participation outcome as "involvement in life situations" (2001), the result of a complex relationship between a person, his or her health condition, and the person's environment (Jette et al., 2008). It is this emphasis on function that this study adopts and seeks to measure in its outcomes assessment, in order to address the needs already identified in the literature and research questions, as well as to address the research priorities identified in the following plea to physiotherapy researchers...

"There is a scarcity of available scientific evidence about the... health care needs of people with disability and about effective interventions for prevention, treatment, and rehabilitation. In addition to the lack of evidence about what works to improve activity and participation of those with disabilities, there also is little evidence about the costs incurred. We encourage scientists conducting research relevant to the nexus of physical therapy and disability to contribute to building this crucial knowledge base. What are the key physical therapy interventions that will improve levels of activity and participation for people with disabilities?" p. 324-5 (Jette and Latham, 2010).

## **Primary Outcome Measure**

In seeking to select outcome measures that will capture data to appropriately answer the research questions, it is important to remember that while a single outcome measure is unlikely to encompass all that requires investigation, the use of multiple outcome measures increases the risk that a statistically significant result may be found by chance with each additional measure undertaken (Freemantle, 2001). This issue is simplified if researchers prospectively identify a primary outcome measure, the specification of which is a key feature of any randomised controlled trial (Freemantle, 2001). A broad range of patient outcomes will be used in order to ensure a comprehensive investigation of the impact of the interventions on patient outcome (please see table 1 for a summary of patient outcome data being collected), and the primary outcome measure will be identified prospectively as suggested.

Health-related quality of life (HRQL) data have been recommended as valid, reliable and responsive outcomes measures for physiotherapists to assess treatment outcomes in patients with a wide range of health conditions (Jette, 1995, Jette, 1993, Resnik and Dobrykowski, 2005, Resnik and Dobrzykowski, 2003). HRQL measures can be generic, condition-specific, or patient-specific instruments, or a combination of instruments (Resnik and Dobrykowski, 2005). This research will use both generic and patient-specific HRQL instruments; condition specific measures will not be utilized due to the inability of different condition specific outcomes instruments to 'talk to each other' (Jette and Haley, 2005).

It is a patient-specific HRQL measure that will be selected as the primary outcome measure for several reasons. Firstly responsiveness - some studies suggest that patient specific instruments may be the most responsive of the HRQL tools, as they specifically addresses problems experienced by the individual patient (Resnik and Jensen, 2003, Stratford et al., 1995). The Patient Specific Functional Scale (PSFS) has shown itself to be more responsive than other established condition-specific measures (Pengel et al., 2004, Cleland et al., 2006, Young et al., 2010). It is the PSFS which will be used for the patients' most disabling functional problems on the basis of this responsiveness, and the three considerations of outcomes measures selection suggested by Jette (Jette, 1993) – psychometric properties, practicality and dimensions selected for measurement. The PSFS possesses established validity across body regions to give numerical rating scores that will be comparable (Brentnall and Sterling, 2007, Chatman et al., 1997, Cleland et al., 2006, Hefford et al., 2009, Hefford et al., 2008, Pietrobon et al., 2002, Sterling and Brentnall, 2007, Stewart et al., 2007, Westaway et al., 1998, Stratford et al., 1995) and the validity studies provide clear data for research purposes on the minimal detectable change (MDC) and the minimal clinically important difference (MCID) which are both reported to be three points for each identified activity and 2 points for aggregate activities (Stratford et al., 1995, Sterling and Brentnall, 2007). From a practical perspective, the PSFS is quick to apply in both the initial and subsequent assessments, is simple to administer and does not require any ranking procedures or software analysis, unlike many disability questionnaires (Brentnall and Sterling, 2007). Finally, the dimensions being measured are activity and participation; the PSFS has been deemed useful in redirecting questioning towards function and ability rather than pain and disability (Brentnall and Sterling, 2007), and in a study which explored how well the PSFS reflected the ICF (Fairbairn et al., 2010), 100% of the analysed items were mapped to the activity, participation, and impairment components of the ICF or overlapped between these components.

### Analysis

The PSFS scores for every consecutive consenting patient of each participating physiotherapist will be analyzed for significant change:

- Total score = sum of the activity scores/number of activities.
- Minimum detectable change (90%CI) for average score = 2 points.
- Minimum detectable change (90%CI) for single activity score = 3 points.

## **Secondary Outcome Measures**

### **1. Generic HRQL**

Generic HRQL instruments are designed for broad use in a variety of patient populations, which is fitting for the broad variety of patients with different musculoskeletal conditions used in this study. The generic instrument selected to measure HRQL in this study is the Euroqol (EQ-5D) on the basis of its broad application to a wide range of health conditions and treatments, and its provision of a simple descriptive profile and single index value for health status (1990, Dolan, 1997, Fransen and Edmonds, 1999, Jenkinson et al., 1997, Polsky et al., 2001, Rabin and de Charro, 2001).

#### **Analysis**

The EQ-5D will be scored as per the standard UK algorithm.

### **2. Self Efficacy**

Successful rehabilitation and expert practice may have additional aspects which are not fully captured by discharge functional or health related quality of life measures (Resnik, 2007). Changes in patient self-efficacy have been hypothesised as another valid outcome measure to use in identifying developing traits of expertise in physiotherapists (Resnik 2007) on the basis that one of the primary goals of rehabilitation that is widely recognized is the enhancement of patient's ability and confidence to manage their own health, particularly in chronic conditions where patients require problem-solving skills and management strategies to handle minor setbacks. Research suggests that activation is developmental and that individuals - on their journey to becoming effective self-managers - pass through different levels of activation (Hibbard et al., 2009). The Patient Activation Measure (PAM) will be used for this on the basis that it has undergone multiphase psychometric testing to confirm its validity and reliability (Agapova et al., 2010, Fowles et al., 2009, Green et al., 2010, Hibbard et al., 2009, Hibbard and Mahoney, 2010, Hibbard et al., 2007, Hibbard et al., 2005, Hibbard et al., 2004, Hibbard and Tusler, 2007) and on the basis that it maintains precision across different demographic and health status groups. The authors identify its use at the aggregate level to evaluate and compare the efficacy of interventions.

#### **Analysis**

The PAM score will be calculated using the standard scoring table, and patients will be classified into one of the four levels of activation outlined in the validity studies for the tool.

### **3. Patient Satisfaction**

One of the key features of development in expertise in clinical reasoning is collaborative reasoning in both diagnosis and management (Edwards et al., 2004, Edwards and Jones, 2007, Jensen et al., 2008) where patient centred care is seen as integral to practice. Indeed, a move toward patient centered care has been recommended by the Department of Health (2007), and has seen the growth of interest in measurement of patient satisfaction as an important outcome measure in healthcare research (Casserley-Feeney et al., 2008). Levels of patient satisfaction would therefore be of interest and the MedRisk Instrument for Measuring Patient Satisfaction With Physical Therapy Care (MRPS) will be used on the basis of its strong psychometric properties assessed on a large, diverse population, its validation for use in an outpatient physiotherapy environment and its user-friendliness, being relatively short (12 items) (Beattie et al., 2005, Beattie et al., 2011, Beattie et al., 2007, Beattie et al., 2002). The availability of the psychometric data, plus the use of negative phrasing, multi-dimensional measurement and Likert scale, and the fact that it is self-completed by

the patient, satisfies the criteria raised by several authors for a suitable patient satisfaction questionnaire (Casserley-Feeney et al., 2008, Hudak and Wright, 2000, Sim and Wright, 2000, Sitzia, 1999).

### Analysis

The MRPS will be scored using the database kindly provided by the MedRisk authors to analyze both internal and external factors affecting patient satisfaction.

### Procedures

It is the *differences* in patient outcomes data that is being measured. Outcomes data will be collected from a cluster of patients being treated by each participating therapist at each stage of the stepped wedge design, giving 4 clusters of patient data per physiotherapist cluster for within group and between group comparison.

For each patient, outcome data will be collected at first and last appointment and at 12 months post discharge. The long term follow up is important in that – as Resnik (Resnik, 2007) points out - it is possible that aspects of physiotherapy intervention (for example, patient education) have health effects which are lifelong and therefore cannot be measured purely with discharge measurements of the patient's status. All patients treated sequentially by the therapist will complete the outcomes until a full data set is obtained.

Patient data loss from failure to complete treatment / DNA will be minimized by telephone contact, having consented patients to being contacted by the researchers by telephone as part of the study follow up. Patients refusing to complete data or withdrawing consent will be reported as will the reasons for failure to complete treatment and / or outcomes.

### Strategies to Enhance Quality of Outcomes

#### Risk Adjustment

To enhance the quality of these outcomes, control of variables that could affect the dependent variables (patient outcomes) is essential before comparing patient outcomes are compared between clusters and within clusters. While no consensus exists for the optimal risk-adjustment method, an approach to risk adjustment has been previously used for outcomes research in physiotherapy (Jette and Jette, 1996; Resnik and Hart, 2003). First, using data from step 1 (before any therapists have commenced intervention) univariate analyses will be used to identify possible confounding variables among patient characteristics (from previous literature, age, severity, sex, onset of condition, number of surgeries for condition, reimbursement, exercise history and employment status).

Next, a general linear model (GLM) will be developed for the HRQL outcome measures—the PSFS and EQ-5D. Each patient characteristic found to be significant in the univariate analyses will be included in the models using a backward-deletion process. General linear models allow for simultaneous control of continuous and categorical variables in the risk-adjustment process. It is the risk-adjusted HRQL data that will be used for all data analysis to analyse the effect of the intervention.

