## **Study Aims & Reasons**

### **Purpose Statement:**

The intent of this study is to assess the effect of work-based facilitation in clinical reasoning on outcomes in musculo-skeletal physiotherapy, to test the theory that clinical reasoning can be nurtured and taught, and that development of this feature of expertise will positively impact patient outcomes.

In the study, validated outcome measures of function, health-related quality of life, symptomology, patient satisfaction and self-efficacy will be used to measure the relationship between facilitation in clinical reasoning via a clinical mentoring programme and patient outcome, while exploring the relationships in the data with the factors of patient age, patient condition, patient prognostic barriers, therapist participation, usual therapist training and organisational context for static musculoskeletal physiotherapists working in a large hospital-based outpatient service.

At the same time, the process of clinical reasoning facilitation will be explored using qualitative interviews with the clinically mentored staff, qualitative interviews with their clinical mentors, and observations of the mentoring process.

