### Eligibility criteria for patient clusters

Consecutive consenting patients attending the outpatient musculoskeletal physiotherapy service at the Cardiff and Vale University Health Board for treatment by the participating physiotherapists during data collection periods towards the end of each step will be eligible to participate. The main exclusion criteria would be patients under 18 years of age, and patients who are not English-literate due to the validity of the Outcome Measures being established only for the English language and for adults.

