### Analysis

The ÖMPQ will be scored and interpreted at the start of treatment as per the scoring instructions:

- For question 1, count the number of pain sites and multiply by two – this is the score (maximum score allowable is 10).
- For questions 2 and 3 the score is the number bracketed after the ticked box.
- For questions 4, 5, 6, 7, 9, 10, 11, 14, 15 and 16 the score is the number that has been circled.
- For questions 8, 12, 13, 17, 18, 19, 20 and 21 the score is 10 minus the number that has been circled.

A total score of 105 or above indicates persons who are at risk of disability or failure to return to work.

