### **Statistical methods**

The analysis of stepped wedge trials has been clearly outlined in a published paper (Hussey and Hughes, 2007) and recommends processes for analysis of cluster-level means and individual level analysis in scenarios where cluster sizes are equal or unequal, and where variance is known or unknown. Processes for between cluster and within cluster analyses are outlined in order to avoid confounding the treatment effect with changes over time; these processes will form the basis for the statistical analysis for the study. If no temporal effects are found influencing the outcome, then a within-cluster analysis can be used to estimate the treatment effect. Statistical analysis will involve a classical ANOVA (so observations belong to one of two groups, each assumed to be independent of the others), supplemented by a random intercept which will reflect systematic differences across different clusters. Similar statistical methods have been used in other published stepped wedge trials (Schnelle et al., 1992, Bailey and Archer, 2004, Mdege et al., 2011).

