## **Variables**

For sake of clarity in the methodological design of this study, the variables require explicit definition. The independent variable will be defined as facilitation in clinical reasoning via a clinical mentoring programme. The dependent variables will be defined as patient outcomes and therapist performance. The control variables will be defined as and usual therapist training, patient age, patient condition, patient prognostic barriers, therapist participation, and organizational context.

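### Patient condition is a declared control variable, but the risk-adjustment candidates omit body region, so a change in regional mix specific to one cluster and step stays unadjusted

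*Protocol*

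**What the plan says.** The Variables section lists the control variables as "usual therapist training, patient age, patient condition, patient prognostic barriers, therapist participation, and organizational context". Condition therefore stands as a separate item from age and prognostic barriers. The Purpose Statement names it too, more loosely, in terms of "exploring the relationships in the data with the factors of patient age, patient condition, patient prognostic barriers".

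The only procedure that adjusts outcomes for patient characteristics is under Risk Adjustment. Step 1 data are screened by univariate analyses, significant characteristics go into a general linear model for PSFS and EQ-5D, and backward deletion follows. The candidates are "from previous literature, age, severity, sex, onset of condition, number of surgeries for condition, reimbursement, exercise history and employment status". The section ends: "It is the risk-adjusted HRQL data that will be used for all data analysis to analyse the effect of the intervention".

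The baseline questionnaire has tick boxes for neck, shoulder, arm, upper back, lower back, leg and other. The only stated use of the sites is in the ÖMPQ scoring rules: "For question 1, count the number of pain sites and multiply by two". The Psychosocial Screening section treats the ÖMPQ as additional to risk adjustment, to be cross-referenced with the outcomes.

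The patients are "Consecutive consenting patients attending the outpatient musculoskeletal physiotherapy service", newly recruited at each step. The effect analysis is an ANOVA "supplemented by a random intercept which will reflect systematic differences across different clusters". The section on challenges of the design adds time effects, while Statistical methods allows a within-cluster analysis if no temporal effect is found.

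**The concern.** A variable declared as controlled should be traceable to an analysis step. Severity, onset and number of surgeries say how bad the problem is, how it began and how far it has been treated. None says which part of the body is affected. The ÖMPQ total would not supply this, because a patient with neck pain only and a patient with leg pain only get the same score on that item.

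The trial pools all musculoskeletal conditions over six sites, grouped into three randomised clusters, and four 12-month steps, with different patients at each step. If expected PSFS change differs by region and the mix of referrals changes at one site pair, part of that change could be read as an intervention effect. Any precision that region offers is also left unused, although the item is already collected.

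**Working it through.** **Inputs from the protocol.** I = 12 physiotherapists in 3 clusters (4 each), T = 4 steps, N = 9 patients per physiotherapist per step, θ = 1, σ_e = 2, τ = 1 (Power calculation summary, Base case details). U = 24, W = 224, V = 56 (Appendix E).

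**Inputs assumed, because the documents give none.** A mean PSFS-change difference of 1 point between two region groups; a shift in mix of 10 to 20 percentage points; region explaining 2 to 5% of residual variance.

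**1. Reproduce the stated power.** With σ² = 4/9 = 0.4444,

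Var(θ̂) = Iσ²(σ² + Tτ²) / [(IU − W)σ² + (U² + ITU − TW − IV)τ²]

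- Numerator: 12 × 0.4444 × 4.4444 = 23.704
- Denominator: 64 × 0.4444 + (576 + 1152 − 896 − 672) = 28.444 + 160 = 188.444
- Var = 0.12579, SE = 0.3547, Δ = 1/0.3547 = 2.8196, power 0.805, total 4 × 12 × 9 = 432

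This matches the protocol.

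**2. How a shift in mix reaches the estimate.** The generalised least-squares estimate in the same model is a weighted sum of cell means. Weights, summed over the four physiotherapists of each cluster:

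| Cluster crossing at | Step 1 | Step 2 | Step 3 | Step 4 | Sum after crossover |
|---|---|---|---|---|---|
| Step 2 | −0.255 | 0.500 | 0.123 | −0.255 | 0.368 |
| Step 3 | 0.000 | −0.377 | 0.377 | 0.000 | 0.377 |
| Step 4 | 0.255 | −0.123 | −0.500 | 0.255 | 0.255 |

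Bias = (sum of weights over the affected cells) × (shift in share) × (PSFS difference between regions).

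- Shift common to all clusters at a step: each column sums to 0, so bias = 0.
- Stable difference in one cluster: the row sums are 0.113, 0 and −0.113. For a 20-point difference, |bias| ≤ 0.113 × 0.20 × 1 = 0.023.
- Lasting shift in one cluster from its crossover on: from 0.255 × 0.10 × 1 = 0.025 to 0.377 × 0.20 × 1 = 0.075. In standard errors this is 0.025/0.3547 = 0.07 to 0.075/0.3547 = 0.21.
- Shift in one cluster at one step only: the largest weight is 0.500, so up to 0.05 (10 points) or 0.10 (20 points), of either sign.
- Shift following crossover in all three clusters: 0.368 + 0.377 + 0.255 = 1.00, so 0.10 to 0.20.

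The zero in the first line depends on keeping the time effects. If they are dropped, as Statistical methods allows, step-wide shifts in mix also enter the estimate, because intervention cells are concentrated in the later steps.

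**3. Precision.** Replace σ_e² = 4 by 4(1 − R²).

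| R² (assumed) | σ² | Var(θ̂) | Δ | Power |
|---|---|---|---|---|
| 0 | 0.4444 | 0.1258 | 2.820 | 0.805 |
| 0.02 | 0.4356 | 0.1234 | 2.847 | 0.812 |
| 0.05 | 0.4222 | 0.1198 | 2.889 | 0.824 |

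**The case against.** The strongest reply has four parts.

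- **Condition is not body region.** The protocol never equates the two, and three of the eight candidates do describe the condition. This stands in part: it would be wrong to infer that patient condition never enters an analysis. What is missing is the kind or location of the problem.
- **The candidate list may be open.** It is given in brackets as drawn from earlier literature, and the full covariate set could be settled in a statistical analysis plan, which was not available here. The Purpose Statement speaks only of exploring. This is fair and keeps the point minor. But the Variables section offers explicit definitions, and the item's only stated use is as a count, so the two sections do not meet as written.
- **PSFS was chosen partly because its scores are comparable across body regions.** That is a property of the scale. It does not show that expected change is equal across regions, and the protocol makes no such claim for EQ-5D.
- **The model already handles mix.** Largely true. A reader might infer that all differences in mix between steps and clusters go unadjusted, or that a shift at one site pair passes in full into the result, giving 0.1 to 0.2 point. The weights above do not support either. The 0.1 to 0.2 is that cluster's own before-after contrast. It would be the bias in the effect only if mix shifted with crossover in all three clusters.

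**Conclusion.** The mismatch is real and minor. Patient condition is declared controlled, the listed adjustment carries it only through severity, onset and surgeries, and the region data on the form are reduced to a count. The exposure that remains is a change in regional mix specific to a cluster and step, plus step-wide changes if the time effects are dropped.

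For a lasting one-cluster shift the bias is about 0.025 to 0.075 point, or 2.5 to 7.5% of the 1-point target. The possible power gain is from 0.805 to about 0.812 to 0.824. Both ranges rest on assumed values (a 1-point difference between regions, a 10 to 20 point shift, 2 to 5% of residual variance); no figure in the protocol shows that region predicts PSFS change. The stated sample size and power are not in question.

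**What to change.** Add one prespecified covariate for grouped pain region to the Risk Adjustment model for PSFS and EQ-5D, built from the sites ticked at baseline: spine only (neck, upper back, lower back), upper limb only (shoulder, arm), lower limb only (leg), and multiple/other. Using all ticked sites matters because the form as shown marks no main site.

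Retain the covariate whatever the step 1 univariate screen shows, and say that this departs from the screen and backward deletion used for the other candidates. That screen rests on only 12 × 9 = 108 patients in the base case. In the Variables section, state that the covariate represents pain region as a proxy for patient condition and is not a diagnosis.

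The cost is about three degrees of freedom and a few lines of text, with no new data collection. The drawback is a heterogeneous multiple/other group, within which region stays unadjusted.
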